### Data Analysis

Descriptive statistics will be used to describe gender, age, and Gross Motor Function Classification System. Primary and secondary outcomes will be analyzed in the same way. The assumption of normality will be checked by visual inspection of the q-q plot and the box plot of the data within groups. A Shapiro-Wilks test will also be performed on the data within groups. The homogeneity of variance will be checked using Levene test.

If the data are normally distributed, an independent *t* test will be carried out for each variable to see if there are differences between the experimental and control groups. The 95% CI for the mean differences will be determined. Pearson *r* will be used to calculate the effect size.

If the data are not normally distributed, a Wilcoxon rank-sum test will be used for each variable to determine if there are any significant differences between groups. Pearson *r* will be calculated as a measure of effect size.

The data analysis will be performed using SPSS (25.00, IBM Corp). For the data analysis, the researchers will use a 95% CI, considering all those variables with a *P* value of less than .05 to be statistically significant.

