### Objectives

The primary aim of this randomized controlled trial is to compare the effect of intensive rehabilitation combined with an isokinetic progressive strengthening program to intensive rehabilitation alone on gait parameters and muscle strength in patients with cerebral palsy. Another goal of this study is to determine whether adding an isokinetic program is more effective than just intensive rehabilitation in decreasing spasticity and improving joint position sense in patients with cerebral palsy.

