### Primary Outcomes

#### Strength

Muscle strength will be assessed with an isokinetic dynamometer (CON-TREX, MJ Multijoint module, Medimex, CMV AG). Patients will be installed as described previously. Patients will perform an aerobic warm-up for 5 minutes and stretching of the quadriceps and hamstring prior to the test. The ROM will be set based on the extension abilities of the patients. Knee flexors and extensors will be assessed in a concentric mode for 3 repetitions at a speed of 30 degrees/s, 5 repetitions at a speed of 120 degrees/s, and for 8 repetitions at a speed of 180 degrees/s; in an isometric mode at 45° of knee flexion for 5 seconds; and in an eccentric mode for 3 repetitions at a speed of 30 degrees/s. The isokinetic equipment is shown in Figure 2.

Between the 2 concentric, the isometric, and the eccentric tests, 90 seconds of recovery will be allowed. Verbal encouragement will be provided for all participants during the entire test. The highest value in Newton-meter, the maximum reached speed in degrees/s, and the total work produced in joules will be considered for data analysis.

A recent meta-analysis from Muñoz-Bermejo et al [6] showed good to excellent levels of reliability of isokinetic dynamometer in measuring knee extensors and knee flexors strength in children with cerebral palsy, with an interclass correlation coefficient (ICC) ranging from 0.7 to 1 in the dominant and the nondominant lower limb.

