#### Gait Assessment

Patients will perform a walking test on the GRAIL (Motekforce Link). The GRAIL technology consisted of a split-belt treadmill with integrated force plates, an incurved virtual reality screen, and a 3D motion capture system (VICON). The treadmill is built with a self-paced mode, allowing patients to walk at a comfortable speed during the entire test.

Spatiotemporal parameters such as gait speed, stride length, step width, and stance time will be recorded during the walking test. Gait speed (m/s) is defined as the average speed recorded during the entire test after removing the first and last seconds to undo the acceleration and deceleration phenomena. Stride length (cm) is defined as the average anteroposterior distance between heel strikes of the same lower limb. Step width (cm) is defined as the average mediolateral distance between both feet. Stance time (s) is defined as the time between heel strike and toe-off from the same lower limb.

Kinematics data will also be collected through the 3D motion capture system. A total of 22 markers will be placed on patients’ lower limbs following the human body model, which has been described as a valid method to measure kinematics [33]. Hip, knee, and ankle ROM will be captured during the entire gait assessment in the sagittal, transversal, and horizontal planes. Electromyography activity will be recorded for both lower limbs using surface electrodes on 2 important muscles. The rectus femoris and biceps femoris will be recorded. These 2 muscles are important for knee function, including extension and flexion.

A 6-minute walking test (6MWT) will also be performed on the GRAIL. The treadmill will be set to the self-paced mode. Patients will be asked to walk during the entire test. The total distance reached during the test will be registered for data analysis. Performing the 6MWT on the GRAIL technology has shown good construct validity and reproducibility [34,35]. The Borg scale will also be measured before and after the 6MWT for every patient as an indicator of the level of exertion perceived during the test [34,35].

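### Roughly 20 or more variables are listed as primary and each is judged at P<.05 with no single endpoint, order or correction, while the sample size covers one unnamed comparison

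*Protocol article*

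**What the plan says.** Under Objectives, the primary aim compares intensive rehabilitation plus isokinetic training "to intensive rehabilitation alone on gait parameters and muscle strength in patients with cerebral palsy". That is two domains, not a variable.

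Under Primary Outcomes, Strength: "Knee flexors and extensors will be assessed in a concentric mode for 3 repetitions at a speed of 30 degrees/s", then at 120 and 180 degrees/s, isometrically, and eccentrically at 30 degrees/s. "The highest value in Newton-meter, the maximum reached speed in degrees/s, and the total work produced in joules will be considered for data analysis".

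Under Primary Outcomes, Gait Assessment: four spatiotemporal variables, then "Hip, knee, and ankle ROM will be captured during the entire gait assessment in the sagittal, transversal, and horizontal planes", then electromyography of two muscles, 6-minute walking distance and the Borg scale.

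Under Data Analysis: "Primary and secondary outcomes will be analyzed in the same way". If data are normal, "an independent *t* test will be carried out for each variable to see if there are differences between the experimental and control groups"; otherwise a rank-sum test is run for each variable. The decision rule is "considering all those variables with a *P* value of less than .05 to be statistically significant".

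Under Sample Size: a two-sided comparison of two independent groups, alpha .05, power .85, effect size 1.1, 15 per group. The effect size comes from a pilot ratio improvement, and the outcome is not named.

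**The concern.** A trial with one primary test at alpha .05 has a 5% chance of a false claim when there is no effect. Here the same threshold is applied separately to every variable in two broad domains, and nothing says which variable, or how many, answers the primary aim. Any variable that crosses .05 can be reported as a significant primary result, and which one is emphasised can be settled after the data are seen. The alpha and power under Sample Size describe one test, so they do not describe the decision set out under Data Analysis.

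At stake is the reading of the trial. The Discussion and Conclusions link positive findings to considering, or possibly implementing, isokinetic training in the care of these patients, without defining a positive finding.

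This is not a detail left to an unseen analysis plan. The article fixes the per-variable rule itself, so a later plan with a hierarchy would contradict the article, not complete it.

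**Working it through.** **1. The plan's own figure.** Inputs (Sample Size): d = 1.1, two-sided alpha .05, power .85. Normal approximation: n per group = 2(z₀.₉₇₅ + z₀.₈₅)²/d² = 2(1.960 + 1.036)²/1.21 = 14.8, so 15. This reproduces the stated 15. With the exact noncentral t, power is 0.83 at 15 per group and 0.85 at 16. The figure is that of a single test at alpha .05.

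**2. Counting the primary variables** (my count; one value per variable, not per limb; Borg left out).
- Peak torque: 5 test modes × 2 muscle groups = 10.
- Spatiotemporal: 4. Six-minute distance: 1.
- Range of motion: 3 joints × 3 named planes = 9. The transversal and horizontal planes are the same plane, so read literally there are 3 × 2 = 6.
- Lean total: 10 + 4 + 6 + 1 = 21, or 10 + 4 + 9 + 1 = 24.
- Fuller total: add maximum speed and total work for the 4 moving modes (8 + 8), giving 26 strength variables, and electromyography of 2 muscles, giving 4 + 9 + 2 + 1 = 16 gait variables. 26 + 16 = 42.

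**3. Chance of at least one P<.05 when nothing differs.** Independent tests: 1 − 0.95^m. For results favouring the isokinetic group only: 1 − 0.975^m. For correlated variables: simulation of t tests with 15 per group and equal correlation between all variables (repeat runs of 20,000 or more differ by about one percentage point). The correlations are assumptions; the article gives none.

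| Variables (m) | Independent | Correlation 0.5 | Correlation 0.8 |
|---|---|---|---|
| 21, any direction | 66% | 44% | 23–24% |
| 24, any direction | 71% | 47–48% | 24–25% |
| 42, any direction | 88% | 59–60% | 30% |
| 21, favouring isokinetic | 41% | 22% | 12% |
| 24, favouring isokinetic | 46% | 24% | 12% |
| 42, favouring isokinetic | 65% | 30–31% | 15% |

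For example, 1 − 0.95²¹ = 0.659 and 1 − 0.95⁴² = 0.884. The expected number of false positives is 21 × .05 = 1.05 up to 42 × .05 = 2.1, whatever the correlation.

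A mixed pattern (assumed: 0.8 within strength, 0.3 within gait, 0.2 between) gives 54% for 24 variables and 61% for 42. Counting only results favouring the isokinetic group, it gives 28% and 32%.

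**4. Remedies at 15 per group, d = 1.1, exact power.**
- One test at .05: 0.83.
- Two tests at .025 each: 0.74 per test; 20 per group would be needed for at least 0.85.
- Fixed order, both at .05: 0.83 for the first. For both to succeed: 0.83 × 0.83 = 0.69 if independent, and at most 0.83, if d = 1.1 holds for both.
- Bonferroni over 24: 0.375. Over 42: 0.31.

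**The case against.** The count is not in the article. Range of motion is described as captured and electromyography as recorded. Only the strength metrics and the 6-minute distance are expressly destined for data analysis. The Strength section also speaks of two concentric tests at one point, although it lists three speeds; dropping one speed from the leanest reading leaves 8 + 4 + 6 + 1 = 19 variables. This stands, so the count should be read as roughly 20 or more and not as an exact number. It does not remove the problem: 1 − 0.95¹⁹ is still 62% under independence.

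The variables are correlated. Ten torques come from the same dynamometer, and speed, stride length and walking distance from the same treadmill. A reader might infer that a false-positive primary result is more likely than not. The documents do not support that without conditions: the chance is below one half for all three counts at 0.8, for the lean counts at 0.5, and in nearly every correlated case if only results favouring the isokinetic group matter.

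A reader might also take "Primary and secondary outcomes will be analyzed in the same way" as abolishing the distinction between primary and secondary outcomes. In context it introduces the normality checks and the choice of test. The weight rests on the P<.05 sentence.

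Finally, a reader might infer that one significant variable counts as success and leads to adoption. The article does not say so. The Discussion speaks of considering a complementary intervention, and the Conclusions use cautious wording; confidence intervals and effect sizes are also planned. What remains is that no other criterion is given.

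**Conclusion.** The point holds. Followed exactly, the plan leaves the error rate for the primary aim uncontrolled, and its sample size refers to a single comparison that the analysis never identifies.

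The inflation is clear under every assumption tried, but its size depends on them: from about 12% (favourable results only, correlation 0.8, lean count) to 88% (any direction, independence, 42 variables), against a nominal 5%, or 2.5% for favourable results alone. Independence is the upper bound and is not realistic here. The values at 0.5 to 0.8 are the more useful guide. Treating limbs separately would raise the count.

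**What to change.** Before outcome data are examined by group:
- Name exactly one strength variable in full: one muscle group, one test mode and speed, one metric, and one limb or a stated limb average. Knee-extensor peak torque in one stated mode would serve. Without the mode and limb, five modes would remain open.
- Name exactly one gait variable, for example gait speed.
- Test the two in a fixed order at two-sided .05, or split alpha between them. Strength before gait would follow the mechanism given in the Background.
- State which variable the effect size of 1.1 and the 15 per group refer to.
- Report all other variables as secondary or exploratory estimates with 95% CIs and without claims of significance.

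Costs: most variables lose primary status. Under a fixed order, gait can be claimed only if strength succeeds (about 0.69 to 0.83 under the assumption above). Split alpha lowers power per test from 0.83 to 0.74. No new patients or measurements are required, but inclusion was due to start in November 2022, so the change may need a documented amendment.

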## Methods

### Study Design

This study will be a prospective randomized controlled trial. Adolescents with spastic diplegia cerebral palsy will be randomized by an independent researcher through a computer-based method into an isokinetic training group (IG) or a control group (CG). The block randomization method will be used to keep the number of subjects in each group equal. The IG will receive a 3-week isokinetic strengthening program together with intensive rehabilitation, and the CG will only follow the intensive rehabilitation. Patients will not be informed if they are part of the intervention or the CG. Outcome measures will be done at baseline (T0) and at the end of the intervention (T1). The protocol has been accepted by the French National Ethics Committee (IDRCB: 2022-A00431-42).

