### Sample Size

Sample size calculation was realized using G*POWER statistical programming (version 3.1.9.2; Franz Faul): power (1−α error *P*)=.85, α=.05, effect size=1.1, with a 2-tailed for a comparison of 2 independent groups. This calculation was based on the results of a pilot study based on ratio improvement following 2 specific interventions in patients with cerebral palsy. It will take 15 participants in each group to complete this study.

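### The analysed quantity (T1 value, change or ratio) is not defined and no baseline adjustment is specified, although the trial is sized on improvement from baseline

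*Protocol article*

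**What the plan says.** Study Design (Protocol article) sets two assessments, T0 before and T1 after the three-week programme, with block randomisation in equal numbers. It states no stratification.

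Sample Size gives "α=.05, effect size=1.1, with a 2-tailed for a comparison of 2 independent groups", at a stated 0.85 that can only be meant as power. On the origin of the effect size: "This calculation was based on the results of a pilot study based on ratio improvement following 2 specific interventions in patients with cerebral palsy". The result: "It will take 15 participants in each group to complete this study".

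Data Analysis applies one method to all primary and secondary outcomes. If the data look normal, an independent t "test will be carried out for each variable to see if there are differences between the experimental and control groups"; otherwise a Wilcoxon rank-sum test is run on each variable. No change score, ratio, covariate or T0 value appears in that section. The outcome sections define the variables as single-occasion measurements: torque, work, gait speed, walking distance, peak resistive torque, repositioning error. They do not say how T0 and T1 are to be combined.

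**The concern.** The sample size speaks of improvement, whereas the analysis speaks only of a variable. Three quite different analyses fit the text: a t test on T1, on T1 minus T0, or on the ratio T1/T0. They differ in power and in how they treat a chance difference between arms at T0. If the choice stays open, it could also be made outcome by outcome after the data are seen.

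This goes beyond detail that a condensed article leaves to a fuller document. The article commits to a test, a fallback, assumption checks and an effect-size statistic, and a plain two-group t test or rank-sum test has no place for a baseline covariate.

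Baseline spread is likely to matter. Participants are aged 11 to 18 with GMFCS levels I to III, and with 15 per arm stable differences between children can swamp a three-week effect unless T0 is used.

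**Working it through.** **Inputs from the protocol.** Effect size d = 1.1, two-sided α = 0.05, power 0.85, 15 per arm (Sample Size). Outcomes at T0 and T1, no stratification stated (Study Design).

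**Assumptions.** The T0–T1 correlation r is not in the protocol, so a range of 0.3 to 0.9 is shown. Ratio improvement is approximated by a difference score with equal variances at T0 and T1. The 1.1 is taken in SDs of that difference.

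**Step 1: the plan's own figure.** By the normal approximation, n per arm = 2(1.960 + 1.036)²/1.1² = 17.96/1.21 = 14.8, so 15, with power 85.4%. By the exact noncentral t, power at 15 per arm is 82.8%, and 16 per arm are needed for 85%. The stated 15 is reproduced to within one per arm. The comparisons below use the exact t, so the benchmark is 82.8%.

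**Step 2: the same effect on each scale.**
- SD(change)/SD(T1) = √(2(1 − r)), so d on T1 alone = 1.1 × √(2(1 − r)).
- ANCOVA residual SD/SD(T1) = √(1 − r²), so d for ANCOVA = d(T1)/√(1 − r²).
- Example, r = 0.8: d(T1) = 1.1 × 0.632 = 0.70, and d(ANCOVA) = 0.696/0.6 = 1.16.
- Degrees of freedom: 28 for the t tests, 27 for ANCOVA.

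| r | d on T1 | Power, T1 alone | Power, change score | Power, ANCOVA | n/arm for 85%, T1 alone | n/arm for 85%, ANCOVA |
|---|---|---|---|---|---|---|
| 0.3 | 1.30 | 93.1% | 82.8% | 95.0% | 12 | 11 |
| 0.5 | 1.10 | 82.8% | 82.8% | 91.8% | 16 | 13 |
| 0.7 | 0.85 | 61.5% | 82.8% | 88.3% | 26 | 14 |
| 0.8 | 0.70 | 45.2% | 82.8% | 86.4% | 39 | 15 |
| 0.9 | 0.49 | 25.6% | 82.8% | 84.6% | 76 | 16 |

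The ANCOVA formula ignores the small loss from chance imbalance in T0. A 20,000-run simulation gives 87.2%, 85.3% and 83.6% at r = 0.7, 0.8 and 0.9, about one point lower. The ordering is unchanged, but at r = 0.9 ANCOVA hardly beats the change score.

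T1 alone and the change score cross at r = 0.5, where √(2(1 − r)) = 1. Below that, T1 alone is the stronger of the two.

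**Step 3: chance imbalance at T0.** The SE of the baseline difference is √(2/15) = 0.37 SD. P(|difference| > 0.5 SD) = 2 × [1 − Φ(0.5/0.365)] ≈ 17% for any one outcome. Given an imbalance of 0.5 SD and r = 0.8:
- T1 alone carries r × 0.5 = 0.40 SD of it into the estimate, against an assumed effect of 0.70 SD on that scale.
- The change score removes the whole 0.5, although only 0.40 carries over. It is off by 0.40 − 0.50 = −0.10 SD.
- ANCOVA removes the expected carry-over.

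**The case against.** A reader might infer that the plan discards T0 and that the trial is therefore underpowered. The text does not support this. Data Analysis leaves the variable undefined and never says that T0 is unused. The sample size, "based on the results of a pilot study based on ratio improvement following 2 specific interventions in patients with cerebral palsy", points towards a comparison of improvement between arms. The objectives also speak of decreasing spasticity and improving joint position sense. A t test on improvement would be consistent with both sections, would use T0 and would keep about 83% power. On that reading ANCOVA gains only about 2 to 6 points by formula for r between 0.7 and 0.9. This objection stands.

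The value of r is also unknown. The cited ICCs, 0.7 to 1 for strength and 0.80 and 0.86 for spasticity, together with the wide age and GMFCS range, make a high r plausible for torque. But an ICC is a reliability figure, not a correlation across an intervention, and no figure is given for joint position sense or for the spatiotemporal and kinematic gait measures. At r = 0.5 or below, T1 alone loses nothing against a change score.

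Nor does chance imbalance make the inference invalid, as a reader might also conclude. Under randomisation both unadjusted comparisons are unbiased over allocations, and the confidence interval covers such imbalance. What is at stake is precision, and accuracy given the imbalance actually observed.

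What the objection does not remove is that the analysed quantity is unstated, and that no reading of the section includes adjustment for a baseline value already collected.

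**Conclusion.** The point holds as a gap in definition and a missed gain in efficiency. The plan fixes an unadjusted two-group test for every outcome, does not name the quantity tested, and specifies no baseline adjustment, although it is sized on improvement.

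The size depends on how the gap is filled. If improvement is tested, the planned power is essentially kept. If T1 alone is tested and r exceeds 0.5, power falls to about 62%, 45% or 26% at r = 0.7, 0.8 or 0.9. ANCOVA is at least as powerful as either unadjusted test over r = 0.3 to 0.9, and it handles chance imbalance better than both.

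These figures rest on an assumed r, on treating the ratio as a difference score with equal variances, and on 1.1 being in SDs of improvement. The pilot's outcome and its exact ratio are not named, so the approximation cannot be checked. Since the same repair serves all three readings, it is worth making before any data are analysed.

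**What to change.** Replace the t test and rank-sum sentences in Data Analysis with wording such as:

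*Each outcome at T1 will be compared between groups by ANCOVA, with group and the T0 value of the same outcome in the model. The adjusted mean difference and its 95% CI will be reported. Positive, skewed measures such as torque and work will be analysed as log T1 on log T0, and the effect reported as a ratio with its 95% CI. If residuals are clearly non-normal, a rank-based ANCOVA will be used.*

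Move the normality and variance checks from the raw data within groups to the model residuals. In Sample Size, name the pilot outcome and say how its ratio was formed. The log-scale effect is close to a ratio of improvement but need not be identical with the pilot's metric.

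The cost is a change of wording and one degree of freedom per model. No new data are needed, and on the assumptions above the 15 per arm can stand.

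### The within-group normality check chooses each outcome's test and estimand at 15 per group, and the rank-sum branch names no effect estimate with an interval

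*Protocol article*

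**What the plan says.** The Data Analysis section of the protocol article applies one rule to all primary and secondary outcomes. Normality "will be checked by visual inspection of the q-q plot and the box plot of the data within groups", with a Shapiro-Wilk test on the same within-group data. Levene's test is also run.

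- **Judged normal:** independent t test, 95% CI for the mean difference, Pearson r as effect size.
- **Judged not normal:** "If the data are not normally distributed, a Wilcoxon rank-sum test will be used for each variable to determine if there are any significant differences", with Pearson r as effect size. No location estimate is named.

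A closing sentence says that a 95% CI will be used, without saying of what, and sets significance at P below .05.

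On size, the Sample Size section gives "α=.05, effect size=1.1, with a 2-tailed for a comparison of 2 independent groups" and concludes: "It will take 15 participants in each group to complete this study". Study Design adds: "The block randomization method will be used to keep the number of subjects in each group equal". It also states that outcomes are measured at both T0 and T1. Neither branch uses T0 as a covariate.

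**The concern.** The outcome data decide what is estimated. One branch targets a difference in means, in Nm, m/s or degrees. The other gives a rank comparison with a P value and a unitless r. The choice is made afresh for each variable, from groups too small for a normality check to separate shapes well.

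The strength domain shows the consequence. Knee flexors and extensors are each tested in five conditions (concentric at three speeds, isometric, eccentric). Peak torque at one speed could appear as a difference in Nm with an interval, and at the next speed as a P value with r. A reader could not compare the two or judge the clinical size of the second. In a trial of 30 adolescents the interval is the most informative result, so losing it for some variables matters.

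**Working it through.** **Inputs.** From the protocol: 15 per group, equal allocation, two-sided alpha .05, power .85 (its label is read as 1−β), effect size 1.1 (read as a standardised mean difference). Assumed: Shapiro-Wilk at .05; failure in either group triggers the switch; the plots are not modelled. The outcome distributions are not given, so a range of shapes is used.

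**1. The plan's own figure.** Normal approximation: n = 2(1.960 + 1.036)² / 1.1² = 17.96 / 1.21 = 14.8, so 15 per group, as stated. By the noncentral t, power at 15 is 0.828, and 16 per group gives 0.853. At 15 per group on normal data, a rank-sum test fixed in advance has power of about 0.80 to 0.81.

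**2. Switching when the data are normal.** P(at least one group fails) = 1 − 0.95² = 0.0975. Peak torque alone gives 2 muscle groups × 5 conditions = 10 variables. Expected switches: 10 × 0.0975 ≈ 1, whatever their correlation. If they were independent, P(at least one switches) = 1 − 0.95²⁰ = 0.64. Correlation would change that last figure.

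**3. Simulation.** 8,000 trials per scenario at 15 per group. The rule is rank-sum if Shapiro-Wilk P<.05 in either group, otherwise the equal-variance t test. The first four result columns are under no effect; power is at a shift of 1.1 SD.

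| Shape | Switches branch | Type I, t test alone | Type I, two-stage rule | Type I of t test, given check passed | Power, t / two-stage |
|---|---|---|---|---|---|
| Normal | 0.097 | 0.048 | 0.049 | 0.048 | 0.832 / 0.832 |
| Uniform | 0.238 | 0.050 | 0.048 | 0.044 | 0.831 / 0.811 |
| Log-normal, sigma 0.25 | 0.274 | 0.051 | 0.053 | 0.053 | 0.828 / 0.838 |
| t, 5 df | 0.282 | 0.047 | 0.047 | 0.050 | 0.836 / 0.866 |
| Gamma(4) | 0.386 | 0.045 | 0.050 | 0.055 | 0.825 / 0.849 |
| t, 3 df | 0.458 | 0.048 | 0.053 | 0.055 | 0.864 / 0.941 |
| Log-normal, sigma 0.5 | 0.623 | 0.044 | 0.052 | 0.067 | 0.830 / 0.902 |
| Exponential | 0.896 | 0.050 | 0.052 | 0.086 | 0.821 / 0.918 |

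The simulation error of a 5% rate is √(0.05 × 0.95 / 8000) = 0.0024. A longer run of 40,000 gave 0.050 for normal data and 0.054 for log-normal sigma 0.5.

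**4. Does the gate protect the t test?** No. Run unconditionally on log-normal data (sigma 0.5), the t test is already at 0.044. Among variables that pass the check it rises to 0.067. The overall rate is the mixture: 0.377 × 0.067 + 0.623 × 0.043 = 0.052.

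**5. How often the branch matters.** The two tests disagree on significance in 1.5% to 3.5% of trials with no effect, and in 5% to 11% at effect size 1.1.

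**6. Precision.** With T0–T1 correlation ρ and equal variances, the residual variance relative to T1 is 1 for a T1 comparison, 2(1 − ρ) for change scores and 1 − ρ² for ANCOVA. Since 2(1 − ρ) − (1 − ρ²) = (1 − ρ)² ≥ 0, ANCOVA is never worse than either, apart from one degree of freedom (30 − 2 = 28 becomes 30 − 3 = 27). The protocol gives no ρ, so the gain is not quantified.

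**The case against.** The strongest defence is that the rule works as a test. Type I error is close to nominal for every shape tried. On normal data power equals that of the t test, and for skewed or heavy-tailed data it is higher, for example 0.902 against 0.830 for log-normal sigma 0.5. That stands. It answers a complaint about error rates, but not the change of estimand or the missing estimate.

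Several stronger readings are tempting and are not supported:

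- *The branch is chosen almost at random.* Only intermediate shapes, with roughly 25% to 60% switching, come near this. Normal data rarely switch and strongly skewed data nearly always do.
- *The rule is an open door to picking the smaller P value.* The text puts the check first and then one test. It does not provide for running both, and it does not say when or by whom the check is made. Within-group checks could be done on coded groups.
- *The rank-sum branch is denied any interval.* The closing sentence on a 95% CI is general. The fair point is that no estimate in that branch is named for it to attach to.
- *The gate prevents baseline adjustment.* It does not. Both named branches simply happen to be unadjusted.

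How the three checks combine when they disagree may be settled in an analysis plan that is not shown, so no weight is put on it. The data-driven choice between two estimands is stated in the article itself and is not an omission.

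**Conclusion.** The point holds as a weakness of prespecification and reporting. At 15 per group the check moves about 10% of normal variables and about 62% of moderately skewed ones to a branch with a different target and no named effect in clinical units. Mixed reporting within one domain is therefore likely: about one of the ten peak-torque variables would be expected to switch even if all were normal. Overall type I error stays near 5% (0.047 to 0.053 in the main runs, 0.054 in the longer skewed run), so neither the validity of the tests nor the sample size is in question.

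The switching rates rest on Shapiro-Wilk at .05, on either group triggering the switch, and on assumed shapes. The plots would move these rates in a direction that cannot be computed. The change is worth making because it is cheap and restores one comparable estimate per outcome.

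**What to change.** Delete the normality gate. For every continuous primary and secondary outcome, prespecify an ANCOVA of the T1 value on group, adjusted for the T0 value of the same variable. Report the adjusted mean difference in original units with its 95% CI and P value. Name one robust standard error in advance, for example HC3, and use it throughout. Keeping all outcomes in original units avoids reintroducing mixed scales within a domain.

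Keep a rank-based analysis only as a sensitivity analysis, which preserves a check under skew. If it is reported, give a Hodges-Lehmann shift with its 95% CI. Use the plots to describe the data and not to select the analysis.

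Cost: a few sentences of analysis wording, slightly more analysis work and one degree of freedom. No new data are needed, because T0 is already collected, and the sample size does not change.
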